### Statistical analysis

We will use two-way repeated measures analysis of variance to test the significance of changes in the number of physically agitated behaviours over time (before, during, after treatment). We will use simple main effects to determine the specific effect of the Montessori intervention relative to the control condition and we will test for the interaction between treatment and time. Simple contrasts will be used to tease out more detailed relationships, including testing the primary hypothesis that Montessori activities reduce the frequency of physically agitated behaviours significantly more than a plausible control condition.

Analysis will be by intention to treat. Baseline characteristics of participants who drop out during the study will be compared to those who complete it to assess patterns of loss to follow-up and provide insights into the degree to which results can be generalised.

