## Methods/Design

### Study design

We will use an efficient, economical design with random allocation to treatment or control conditions followed by cross-over. Repeated measures RCTs minimise intra- and inter-individual differences since all participants are subject to both conditions and behaviours vary greatly in frequency within and between people with dementia from hour to hour and day to day [14].

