### Interventions

Treatments should be applied over a sufficient number of days to account for random "noise" but not extend for so long that participation is compromised by disease progression, inter-current illness and unavoidable changes to psychotropic medications. Our selected period of four weeks is a reasonable compromise. Similarly, individual sessions should be long enough to detect real changes in behaviour before, during and after sessions but not so long that observations are likely to be interrupted by meals, nursing interventions and visitors. Ninety minutes is the longest feasible period in our experience. Consented, willing participants will be assigned in random order to Montessori or control blocks for two weeks then switched to the other condition. Interventions, whether Montessori or control, will be delivered twice weekly at times when nursing staff report that target behaviours are most likely to be present (excluding times of personal nursing care). Interventions (Montessori or control) will be delivered for 30 minutes per session. Observations will be made for 30 minutes before, 30 minutes during, and 30 minutes after interventions, giving a total observation period of 90 minutes per session, and 12 hours overall per person.

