### Outcomes measures

A discretely positioned, trained researcher will record if the selected physically agitated behaviour is present or absent at one-minute intervals over the three 30-minute observation periods giving 30 data points per period and 90 per session. Behaviour counts will range from zero to 30 per period. This method was used successfully in previous studies with very high levels of inter-rater reliability [17,26-29].

The *primary *measure in this trial will be the change in mean counts of the target physically agitated behaviour across before, during and after intervention phases.

*Secondary *measures will include:

(a) Rating scales completed by the observing researcher during the 30 minute treatment periods at one-minute intervals of the participant's predominant levels of engagement and affect.

We distinguish between four types of engagement based on the Menorah Park Engagement Scale [30]: 1) non-engagement, which is described as a blank stare or engagement with something else than the facilitator and/or the presented activity; 2) self-engagement, engagement with the self, including engagement displayed when a person shows agitated behaviours, e.g. wandering, repetitious behaviour (wringing hands); 3) passive engagement, the person is watching or listening to the facilitator or activity; 4) constructive engagement, the person is actively involved with the facilitator or activity, e.g. by speaking to the facilitator or handling materials used in the activity (folding towels or leafing through a book).

For each minute the predominant type of affect is noted. We will include three positive emotions (pleasure, contentment and interest), one neutral and three negative emotions (anger, sadness and fear/anxiety).

(b) The 29-item Cohen-Mansfield Agitation Inventory [22] completed by the researcher in discussion with nursing staff in closest contact with the resident at the end of each two-week period, relating to behaviour in the preceding fortnight. Where possible, the same staff members will be questioned on each of the four occasions.

(c) A global rating by the residential managers of satisfaction with the outcome of the trial.

(d) The time and costs involved in preparing Montessori activities.

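### The stated two-way ANOVA leaves out cross-over period and randomised order; adding them is a nearly free improvement that protects some, not all, of the planned contrasts.

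*Protocol article*

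**What the plan says.** The Study design section describes "random allocation to treatment or control conditions followed by cross-over", and the Interventions section adds: "Consented, willing participants will be assigned in random order to Montessori or control blocks for two weeks then switched to the other condition". This is a two-sequence, two-period cross-over in which order is what is randomised. The ratio of the two orders is not given.

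The Statistical analysis section names the model: "We will use two-way repeated measures analysis of variance to test the significance of changes in the number of physically agitated behaviours over time". The same sentence spells out what is meant by time: "changes in the number of physically agitated behaviours over time (before, during, after treatment". So time there means phase within a session, not first versus second fortnight. The other factor is treatment. Two effect tests are then named. The first compares conditions within a phase: "We will use simple main effects to determine the specific effect of the Montessori intervention relative to the control condition". The second asks whether that comparison differs between phases, in the words "we will test for the interaction between treatment and time". Simple contrasts are to test the primary hypothesis, but the section does not say which ones. Period, sequence and order do not appear.

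The Outcomes measures section defines the primary measure as "the change in mean counts of the target physically agitated behaviour across before, during and after intervention phases". Each session therefore carries its own before level.

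**The concern.** In a two-period cross-over each resident's Montessori-minus-control difference also contains the difference between the second block and the first, with a sign that depends on order. If the model has no period term, that component goes into the residual. If the two orders are of unequal size, part of it also goes into the estimated treatment effect. At stake are some power and, for an uneven split, a bias in those contrasts that a between-block change can reach.

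**Working it through.** **Inputs.** From the Sample size calculation section: SD 2.15, improvements of 1.53 and 0.69 counts, within-person correlation 0.70, two-sided alpha 0.05, power 90%, n=70, 80 recruited with 10% attrition. Assumed, because the article gives neither: a period shift π of 0.42 to 1 count, and order splits of 35/35 and 42/28.

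**The plan's own figure.** The difference is 1.53 − 0.69 = 0.84 counts, and 0.84/2.15 = 0.39. For a paired difference with SD s, n = (1.960 + 1.282)² s²/0.84² = 10.51 s²/0.7056.
- Correlation 0.70: s = 2.15 × √(2 × 0.30) = 1.665, so n = 41.3, i.e. 42.
- s = 2.15 (equivalent to correlation 0.5): n = 68.8, or 69.1 with the rounded 0.39, i.e. 70.

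The stated 70 follows from the second SD and not from the stated correlation. That is a separate point; here both SDs are carried.

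**Model.** Let D be a participant's Montessori-minus-control difference in the contrast analysed, τ its true mean and π the shift of that contrast from block 1 to block 2. Then D has mean τ + π with control first and τ − π with Montessori first. Let p be the share with control first. Without a period term:
- bias = (2p − 1)π
- variance of D = s² + 4p(1 − p)π²

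**Within-phase contrast (condition compared during the session), 35/35, n=70, noncentral t:**

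| SD of difference | Shift | Variance increase | Power, no period term | Power, period term |
|---|---|---|---|---|
| 2.15 | 0 | 0% | 89.7% | 89.7% |
| 2.15 | 0.42 | 4% | 88.6% | 89.7% |
| 2.15 | 0.84 | 15% | 85.1% | 89.7% |
| 2.15 | 1.0 | 22% | 83.2% | 89.7% |
| 1.665 | 0 | 0% | 98.6% | 98.6% |
| 1.665 | 0.42 | 6% | 98.1% | 98.6% |
| 1.665 | 0.84 | 25% | 96.0% | 98.6% |
| 1.665 | 1.0 | 36% | 94.6% | 98.6% |

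Example of the variance column: 0.84² / 2.15² = 0.706/4.62 = 0.15.

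At 35/35 there is no bias and the unadjusted test is conservative: with a 1-count shift and SD 1.665, simulated type I error is about 2.4%. At 42/28, p = 0.6 and the bias is 0.2 × 1 = 0.20 counts, which is 24% of 0.84; simulated type I error is about 10%.

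**Treatment-by-phase contrast (difference of before-to-during changes).** If block 2 moves before and during counts by the same π, each change score moves by π − π = 0. In simulation (5,000 trials, all correlations 0.70) a 1-count shift in every phase left the null mean at 0, the SD at 2.35 and type I error at about 5%, at 35/35 and at 42/28. A trend in the change itself does not cancel. For 0.5 count, the SD rises from 2.35 to 2.40 at 35/35; at 42/28 the bias is 0.2 × 0.5 = 0.10 counts and type I error is about 6%.

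**The case against.** The strongest reply is that the primary measure is a within-session change, so the before observation already removes block-to-block differences in level. That stands for the treatment-by-phase interaction. A reader might infer that any trend between blocks damages the primary result; the article does not support this. The reply does not cover the simple main effects, which compare conditions within a phase. Nor is the primary hypothesis tied to the interaction: it is left to unspecified simple contrasts.

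A reader might also take the Interventions section as predicting time trends. It says that treatment should not last so long that "participation is compromised by disease progression, inter-current illness and unavoidable changes to psychotropic medications", and this is the reason for stopping at four weeks. It names possible sources of change but forecasts none.

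A third tempting reading is that the standard error and p-value are invalid. They are not in general. With unrestricted random order, the chance imbalance is already part of s² + π². In simulation with 72 completers and a shift of 0.84, type I error was 5.0% (SD 1.665) and 4.8% (SD 2.15), with mean bias about 0. To count that imbalance again as a separate bias would be double counting. If all 8 expected dropouts came from one order (40/32), the bias would be 8/72 × 0.84 = 0.09 counts, 11% of the planned effect, with type I error of 4.6–4.7%. A 42/28 split is more uneven than the planned attrition produces from balanced orders, although simple randomisation of 70 gives a split at least that uneven about 12% of the time.

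Finally, this is a condensed article, and a fuller analysis plan may carry a period term. But the article does more than stay silent: it states a two-way model and names both factors.

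**Conclusion.** The point holds in a limited form. The stated model omits the period and sequence structure that randomising order creates, and this exposes the within-phase simple main effects to level shifts and the interaction contrast to trends in the change. For shifts of 0.42 to 0.84 counts with equal orders, the loss on the during-phase contrast is about 1 to 5 percentage points of power at SD 2.15, and 0.5 to 2.6 points at the stated correlation of 0.70, where power stays above the planned 90%. Bias needs both unequal orders and a shift in the contrast analysed. All of this rests on assumed shifts and splits; an upper shift equal to the whole planned treatment difference has no basis in the article. This is a worthwhile, nearly free improvement, not a defect that must be repaired before the trial can be interpreted.

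**What to change.** State the analysis as a cross-over: a mixed model with fixed effects for condition, phase, condition-by-phase, period, period-by-phase and sequence, and a random participant effect. Name the primary contrast and test it from this model. Phase and condition-by-phase have to stay, because without them the model cannot estimate the primary measure.

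A simpler route to the same estimate is to compute each participant's block-1-minus-block-2 difference in the primary change score and compare it between the two orders. Half the difference in group means is the treatment effect. It equals the equally weighted average of the Montessori-minus-control means in the two orders. Do not pre-test for carry-over.

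The cost is one sentence, no new data and about one degree of freedom for the contrast (69 to 68 at n=70). At 35/35 power is unchanged at 89.7% or 98.6%. At 42/28 with no shift, adjustment costs little: 89.7% becomes 88.4% (SD 2.15) and 98.6% becomes 98.3% (SD 1.665).

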### Sample size calculation

Sample size was calculated for the primary outcome measure (physically agitated behaviour) for a two-sided hypothesis test with a Type I error rate of 0.05 and a Type II error rate of 0.10 (90% power). In the 30-minute baseline observation period, we anticipate that participants will display a mean count of 5.0 physically agitated behaviours (maximum 30) with a standard deviation of 2.15. We anticipate a mean improvement of 0.69 behaviours per period during the control condition (effect size 0.32) compared with a mean improvement of 1.53 per period during Montessori activities (effect size 0.71), giving a difference of 0.39 between the conditions. Based on data from the study by Garland *et al*. [17], we estimate a within-person correlation of 0.70. A sample of 70 participants will be required to detect this difference, assuming the same variance (SD = 2.15) across conditions. Based on previous experience, and the relatively brief duration of this study, we expect 10% attrition and so will recruit 80 participants.

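### Testing Montessori through change from the before-phase costs precision in this cross-over; adjusting for the within-person before-phase difference would be at least as precise on the same data

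*Protocol article*

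**What the plan says.** The Interventions section sets the same observation scheme for every session in both conditions: "Observations will be made for 30 minutes before, 30 minutes during, and 30 minutes after interventions". The Outcomes measures section defines the primary measure as "the change in mean counts of the target physically agitated behaviour across before, during and after intervention phases".

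The Sample size calculation is also framed as improvement from baseline: a "mean improvement of 1.53 per period during Montessori activities (effect size 0.71") is set against a "mean improvement of 0.69 behaviours per period during the control condition (effect size 0.32"), "giving a difference of 0.39 between the conditions". It gives a single within-person correlation, 0.70, and does not say which two measurements it links.

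The Statistical analysis section plans a two-way repeated measures analysis of variance in which before, during and after are levels of the time factor. It lists simple main effects for Montessori relative to control, and adds that "we will test for the interaction between treatment and time". The primary hypothesis is assigned to simple contrasts that are not written out. No covariate is named.

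**The concern.** In this model, a greater improvement under Montessori is the contrast (during minus before, Montessori) minus (during minus before, control). The before count enters with its coefficient fixed at 1.

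In a parallel-group trial that subtraction can remove much of the variation between people. Here the cross-over has already removed it, because both conditions are observed in the same person. What remains in the before counts is occasion-to-occasion fluctuation, and the Study design section itself says behaviour fluctuates widely over hours as well as days. Subtracting a second pair of noisy 30-minute counts then adds variance, unless the before and during counts of one session move together closely. Using the before count as a covariate lets the data choose the weight.

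At stake are the precision of the main result and, under some correlations, the planned 90% power.

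**Working it through.** **Inputs from the Sample size calculation.** Two-sided alpha 0.05; 90% power; "a mean count of 5.0 physically agitated behaviours (maximum 30) with a standard deviation of 2.15", taken as the SD of each analysed count; improvements 1.53 and 0.69; correlation 0.70; n = 70.

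**Assumptions.** The 0.70 is applied to any two counts from different conditions. The before-during correlation within a session, r_s, is not in the protocol, so 0.70 to 0.90 is shown.

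**The plan's own figure.** The difference is 1.53 − 0.69 = 0.84 behaviours, and 0.84/2.15 = 0.39, so the stated 0.39 is in SD units. With a normal approximation, n = (1.960 + 1.282)² × V/0.39², where V is the variance of the tested contrast in units of SD².

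- V = 1 (paired difference with SD 2.15): 69.1, so 70. This reproduces the stated figure, but does not use the 0.70.
- V = 2(1 − 0.70) = 0.6 (one paired difference): 41.4, so 42.
- V = 4(1 − 0.70) = 1.2 (difference of two changes, all correlations 0.70): 82.9, so 83.

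The stated 70 therefore does not show which contrast was powered.

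**Variance of the two contrasts.** Let D_during and D_before be the within-person Montessori-minus-control differences.

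- V_D = 2 × 2.15² × (1 − 0.70) = 2 × 4.6225 × 0.30 = 2.77, for either difference.
- Cov = 2 × 2.15² × (r_s − 0.70).
- Change contrast: 2V_D − 2Cov.
- Covariate-adjusted contrast: V_D × (1 − k²), with k = Cov/V_D = (r_s − 0.70)/0.30.
- Ratio, change to adjusted: 2/(1 + k). This is never below 1 and depends on neither the SD nor the effect size.

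Power below is t-based, at n = 70 and a difference of 0.84.

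| r_s | k | Variance, change | Variance, adjusted | Ratio | Power, change | Power, adjusted |
|---|---|---|---|---|---|---|
| 0.70 | 0 | 5.55 | 2.77 | 2.0 | 84% | 98.6% |
| 0.80 | 0.33 | 3.70 | 2.47 | 1.5 | 95% | 99.3% |
| 0.85 | 0.50 | 2.77 | 2.08 | 1.33 | 98.6% | 99.8% |
| 0.90 | 0.67 | 1.85 | 1.54 | 1.2 | 99.9% | above 99.9% |

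Between the first two rows, the change contrast has 89.7% power at r_s = 0.75 and 90.8% at 0.76, so the crossing point is about 0.76. At r_s = 0.70, 90% power needs 85 people for change and 44 for the adjusted contrast (t-based).

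**How the covariate is entered.** The adjusted column regresses D_during on D_before. Entering the raw before count in a model with a random participant intercept is not equivalent, because its slope is pulled toward the between-person association. Simulations with n = 70 gave these variances relative to the change contrast:

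- r_s = 0.70: about 0.70 to 0.75 with the raw count, against 0.50 in theory for the within-person difference.
- r_s = 0.85: about 0.85 to 0.88, against 0.75 in theory.

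These are rough figures: one check used 300 trials without period or sequence terms, and some fits gave convergence warnings.

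**Same target.** Without carry-over, both methods averaged 0.39 SD in simulation (10,000 trials of 70). A 0.1 SD carry-over into the Montessori before-phase moved the change estimate to 0.29. The adjusted estimate stayed at 0.39 with k = 0 and moved to 0.35 with k = 0.4.

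**The case against.** The strongest reply concerns attribution. The interaction test is one of three listed items, and the primary hypothesis is assigned to simple contrasts that are not spelled out. A simple effect of condition at the during level subtracts nothing; with all correlations at 0.70 its power at n = 70 is 98.6%, the same as the adjusted contrast. This stands as a limit. The change-based primary measure and the improvement-based sample size point to the change contrast, but do not prove that it is the primary one.

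The second reply concerns power. A reader might infer that 70 people cannot give 90% power. The protocol does not support that, because the before-during correlation is not among its inputs. Adjacent half-hours of one session would normally correlate more than counts from different fortnights, and about 0.06 above 0.70 is enough to restore 90%. This reply also stands. It leaves the variance penalty in place across the range shown.

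Third, repeated measures analysis of variance on these counts is a valid analysis, and only efficiency is in question. That is correct, and it sets the weight of the point.

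**Conclusion.** The point holds as a loss of efficiency. If the primary contrast is change from the before-phase, its variance is 1.2 to 2.0 times that of the covariate-adjusted contrast for same-session correlations from 0.90 down to 0.70. Power falls below the planned 90% only under about 0.76.

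Two stronger readings are not supported. The protocol does not name the interaction as its primary test. Nor is halving the variance the expected gain: that figure belongs to the case where the single 0.70 applies to every pair of counts, and it is not reached with a raw before count in a random-intercept model.

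The result rests on equal SDs of 2.15, cross-condition correlation 0.70, an assumed range for the same-session correlation, and large-sample behaviour of the covariate slope. That both methods estimate the same effect also requires before-phases unaffected by condition. With two sessions a week for two weeks, sessions two to four of each block follow earlier sessions of the same condition, so this is a real assumption. If it fails, the change contrast is distorted more.

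**What to change.** Write out the primary contrast as the during-phase count, Montessori against control, adjusted for period and for the within-person before-phase difference. This can be done by centring each before count on the person's own mean, or by fitting participant as a fixed effect; the raw before count with a random intercept recovers only part of the gain. Analyse the after-phase count in the same way and report the treatment-by-time interaction as supportive. State the assumption that before-phases are not affected by condition within a block.

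The cost is analysis wording only. Before counts are already collected in every session, so there are no new data, visits or participants.

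### The named repeated-measures ANOVA cannot keep every randomised participant, so the stated intention-to-treat analysis needs a method that can, or a complete-case label

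*Protocol article*

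**What the plan says.** All references are to the protocol article.

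- **Design (Interventions).** Participants are "assigned in random order to Montessori or control blocks for two weeks then switched to the other condition". Sessions "will be delivered twice weekly at times when nursing staff report that target behaviours are most likely to be present", so there are 2 × 2 = 4 per condition and 8 in all.
- **Primary measure (Outcomes measures).** It is the "change in mean counts of the target physically agitated behaviour across before, during and after intervention phases".
- **Method (Statistical analysis).** The article writes: "We will use two-way repeated measures analysis of variance to test the significance of changes in the number of physically agitated behaviours over time". The primary hypothesis, Montessori against control, is tested by contrasts within that analysis.
- **Principle (same section).** "Analysis will be by intention to treat".
- **Drop-outs (same section).** "Baseline characteristics of participants who drop out during the study will be compared to those who complete it". The stated purpose is to describe patterns of loss and judge generalisability. No imputation or likelihood-based method is named.
- **Attrition (Sample size calculation).** 70 participants are required, and "we expect 10% attrition and so will recruit 80 participants".

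**The concern.** The method and the principle are stated side by side and do not fit together as written. Classical two-way repeated-measures ANOVA splits up the variation within a complete set of cells per person. With two conditions and three phases there are six cells, and a person with an empty cell cannot enter. Someone who leaves before the switch has no data for the second condition, so three cells are empty. The principle keeps that person and the named method drops them. Comparing the baseline characteristics of drop-outs and completers describes the loss but returns nobody to the test.

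At stake is a headline result labelled intention to treat that would describe only people observed in both blocks. Loss need not be random. The Interventions section itself names disease progression, intercurrent illness and changes in psychotropic medication as threats to participation. Under Ethical considerations, taking part depends on continuing assent, shown by willingness to join the activities. If people whose behaviour was worse in the first block are more likely to leave, a complete-case comparison can be biased even though the data that predict the loss were recorded.

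**Working it through.** **1. The plan's own figure.** Inputs from Sample size calculation: two-sided α 0.05, power 90%, difference 0.39 in SD units (1.53 − 0.69 = 0.84 counts; 0.84/2.15 = 0.39). Taking 0.39 directly as the standardised paired difference:

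n = (1.960 + 1.282)² / 0.39² = 10.51 / 0.1521 ≈ 69.1, so 70 (72 by the exact t calculation).

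Allowing for attrition, 70/0.9 = 77.8, so 78, which the article rounds up to 80. At 10% loss, 80 × 0.9 = 72 remain.

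**2. Who would leave the ANOVA.** At most, all drop-outs: 80 − 72 = 8 (10%). Because the cells are means over up to four sessions, someone who leaves during the second block can still have all six. Assume a constant drop-out hazard over eight sessions that totals 10%:

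- No session in the second block (0 to 4 completed): 1 − 0.9^(5/8) = 0.064; × 80 ≈ 5.1.
- Leaving during the second block (5 to 7 completed): 0.9^(5/8) − 0.9 = 0.036; × 80 ≈ 2.9.
- Within the first group, no session at all: 1 − 0.9^(1/8) = 0.013; × 80 ≈ 1.0.

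So about 5 of 80 are necessarily lost and 8 is the upper end. About 1 would have no data under any method.

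**3. Power.** At a standardised difference of 0.39 (noncentral t), power is 0.904 with 72 and 0.931 with 80. The issue is not power.

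**4. Bias when loss depends on observed counts (illustration).** Assumptions: one outcome per condition, SD 2.15, the article's correlation of 0.70 applied between conditions, a true difference (control minus Montessori counts) of 0.84, 40 people per order, and the eight control-first participants with the highest first-period counts leaving at the switch.

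- Mean of the top fifth of a standard normal: 0.280/0.2 = 1.40.
- Mean of the remaining 32: −8 × 1.40/32 = −0.35 SD.
- Their expected difference: 0.84 + 2.15 × (1 − 0.70) × (−0.35) = 0.84 − 0.226 = 0.614.
- Complete-case estimate: (32 × 0.614 + 40 × 0.84)/72 = 0.74.

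Simulation of this scenario agrees: complete cases give about 0.75, and a mixed model using all observed data gives 0.84, the true value. The scenario is deliberately one-sided. The same kind of loss among Montessori-first participants shifts the estimate the other way, so loss balanced over the two orders would largely cancel.

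**5. Where the mixed model does not help.** Suppose instead that the eight lost have a true difference of 0, unrelated to anything observed. The all-randomised effect is then 72/80 × 0.84 = 0.756. In simulation complete cases give 0.84 and the mixed model 0.82. People seen in one condition add little to a within-person contrast, and the model cannot recover an effect that was never observed.

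**The case against.** The strongest reply is that the article never mentions listwise deletion or a completer set. Repeated-measures ANOVA and intention to treat are compatible if empty cells are imputed, and an imputation rule may sit in a full protocol or analysis plan that is not shown. This stands as a limit on the conclusion: one cannot say that the trial will exclude these people, only that the method and principle as published do not fit and nothing in the article bridges them.

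Several stronger readings are tempting, and the document does not support them:

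- **That recruiting 80 to have 70 proves a completer analysis.** Inflating for attrition is routine under any method, including mixed models, because drop-outs carry less information. It does not show who is analysed.
- **That any missed session removes a participant.** The outcome is defined through mean counts and the ANOVA is two-way, so sessions are not a repeated factor. A single missed session empties no cell.
- **That the effect would be overstated by a known amount, which a mixed model would remove.** That needs an assumed effect among the people lost. In the zero-effect example above, the model barely changes the answer.
- **That giving each person's means equal weight is an error.** It is a legitimate choice and separate from this point.

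The design also limits missing data. Under both the Montessori and the control intervention, the facilitator stays with a participant who cannot be engaged, so non-engagement alone need not lose a session. Withdrawal of assent, illness or death still can.

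**Conclusion.** The point holds in a limited form. The article names a primary method that cannot use a participant with an empty condition-by-phase cell, states intention to treat, and gives no means of reconciling the two. Unless some rule outside the article fills those cells, the primary test would be a complete-case analysis under an intention-to-treat label. About 5 to 8 of 80 randomised participants (6% to 10%) would be left out, mainly those who leave before the second block. This rests on the article's 10% attrition and, for the lower figure, on drop-out spread evenly over sessions. The loss of power is slight. Bias is possible where loss depends on earlier observed counts: in a one-sided illustration, complete cases gave about 0.75 against a true 0.84. Neither its size nor its direction can be predicted from the document. This should be fixed, because it concerns the primary test and its label, but the expected loss is small and the design is unaffected.

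**What to change.** Make the primary analysis a mixed model on the counts already recorded, at session level or as condition-by-phase means. Use fixed effects for condition, phase, condition-by-phase and period, and a random participant effect, with session within participant added for session-level data. Include every randomised participant with any observed session, under the assigned order. Test the primary hypothesis by the corresponding contrast, and keep the repeated-measures ANOVA on completers as a sensitivity analysis. If the ANOVA is to stay primary, state how empty cells are filled, or call the analysis complete-case.

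The cost is a change of wording and slightly more analysis work, with no new data collection and no change to the sample size. The model relies on data being missing at random given what was observed. It does not correct loss that depends on unobserved effects, and it cannot include the roughly one person in 80 who may leave before any session. The comparison of drop-outs with completers remains useful and should be kept.
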